## Abstract

**Background:**

Patients requiring hemodialysis (HD) often have several chronic comorbidities, which necessitate the use of several medications and hence put them at high risk of polypharmacy. Medication-related problems (MRPs) among HD patients are a serious issue as they can increase morbidity and nonadherence with medications. To overcome this issue, a unique pharmacy practice model including medication review (MR) and motivational interviewing (MI) is needed to improve medication adherence, by reducing MRPs and optimizing therapeutic outcomes. The present study aims to assess the effectiveness of MR and MI in improving medication adherence, quality of life (QOL) and clinical outcomes among end-stage renal disease (ESRD) patients who are on dialysis.

**Method and design:**

This pre-post study will be conducted prospectively among patients with ESRD who have been on dialysis at the Hemodialysis Unit, Hospital Kuala Lumpur and the Hemodialysis Affiliated Centers of the University Malaya Medical Centre, from August 2020 till August 2021. Medication adherence will be assessed using the General Medication Adherence Scale (GMAS), whilst patients’ HRQOL will be assessed using the Kidney Disease Quality of Life Short Form 36 (KDQOL-36). Clinical parameters such as blood glucose level, calcium, phosphate, hemoglobin and serum low-density lipoprotein (LDL) levels will be obtained from medical records. A total of 70 patients will be recruited.

**Discussion:**

We hypothesize that the implementation of pharmacy-based MR and MI may expect an increase in medication adherence scores and increase in HRQOL scores from baseline as well as achieving the clinical lab parameters within the desired range. This would indicate a need for a pharmacist to be involved in the multidisciplinary team to achieve a positive impact on medication adherence among hemodialysis patients.

**Trial registration:**

Ethical approval has been obtained from the National Medical Research and Ethics Committee NMRR: 20-1135-54435 and Medical Research Ethics Committee, University Malaya Medical Centre MREC ID NO: 202127-9811.

## Introduction

The Global Burden of Disease study (2010) ranked chronic kidney disease (CKD) as the 27th highest cause of total global deaths in 1990, and the 18th highest in 2010 [1]. In Malaysia, a total of 31,497 of patients went for HD in 2014, compared to 29,192 patients in 2013. According to the Malaysian Dialysis and Transplant Registry 2018, the number of new dialysis patients has increased yearly with 8431 new cases reported (an increase of 5%) in 2018. An improvement in the survival rates of patients with ESRD can be seen, due to advances in dialysis treatment [2]. However, the mortality rates for patients with ESRD on chronic dialysis remain high [3] due to the presence of inflammation, undernutrition, and heart-related problems [4, 5].

In addition, ESRD patients who are on dialysis show an impaired quality of life [6]. This is because these patients are not able to accept their disease state, since undergoing renal replacement therapy may make them feel stigmatized or pressured as they are not as "normal" as their friends [7, 8] besides the extensive time spent in dialysis, high expenses and lifestyle restriction to diet and fluid intake, also becomes the contributing factors of low quality of life among HD patients [9]. Generally, the health-related quality of life (HRQOL) refers to the physical, psychological, and social functioning of a person [10]. It is a significant marker of how the ESRD patients are coping with their disease [11]. Assessing health-related quality of life can show the degree of burdens in the ESRD patients [2]. A cross-sectional study showed that ESRD patients who are on dialysis reported to have highly impaired HRQOL, both physically and mentally [12]. Thus, it is vital to identify the potential determinants for lower quality of life to ensure appropriate intervention is being made.

Patients requiring HD often have several chronic comorbidities, which necessitate the use of several medications and hence put them at high risk of polypharmacy. Subsequently, the prevalence of polypharmacy (use of 5 or more medications) among patients requiring HD is high, which leads to medication-related problems, especially in ESRD patients who are on dialysis. It is estimated that at least one MRP is identified for every 15.2 drug exposures [13]. MRPs among ESRD patients who are on dialysis are a serious issue as they can induce morbidity, and nonadherence to prescribed oral medications. Poor compliance and nonadherence are a public health issue in which a patient’s beliefs and myths such as uncertainty on the efficacy of the treatment; nonacceptance of the disease; disbelief in the diagnosis plays a role in shaping their attitude and practice toward medications. Moreover, lower socioeconomic status and educational level are the contributing factors to nonadherence as well [14]. Studies shown that an average prevalence rate of 52.5% medication non- adherence was reported among HD patients [15].

Thus, adherence to medication therapy is a key component of the effective management of dialysis patients. The pharmacist plays a crucial role in identifying MRPs associated with polypharmacy and suggests appropriate interventions to optimize patient outcomes. Moreover, including pharmacists in multidisciplinary team rounds, pharmacist activity such as medication therapy management, medication review and reconciliation as well as deprescribing [16] have proven to improve patient’s adherence to their medications and dietary regimens by minimizing polypharmacy [17]. However, for interventions that are complex and require lifestyle modifications it is worth addressing patients’ beliefs and intentions to perform action. A more comprehensive approach entails a full review of drug regimens and patient attitudes are needed rather than patient education or counseling alone [18].

Therefore, recommendations involving complex behavior change through MI are required. Motivational interviewing is a skillful clinical method, a style of counseling and psychotherapy that is widely used in medical settings to promote autonomy for self-direction based on patient goals and values [19]. A pharmacy-based MI and review program have an important impact on the care of hemodialysis patients by reducing the number of MRPs.

Information about the quality of life and adherence among hemodialysis patients in Malaysia is limited to reporting the incidence rate. To date, there is a paucity of information regarding the effectiveness of reducing MRPs and improving adherence using MI techniques among ESRD patients who are on dialysis [20]. In addition, there is no MI component in the renal medication therapy adherence clinic practice. The relationship between MRPs and QOL among HD patients has rarely been studied in Malaysia. Moreover, a previous study on improving adherence among HD patients uses only one component, either MR or MI, to show effectiveness. To date, no study has used a combination of these two interventions to create sustainable behavioral change for adherence to medication. **Hence, this study will evaluate the effectiveness of MR and MI in improving dialysis patients’ adherence, QOL and clinical outcomes.**

## Materials and methods

### Study design

A pre-post study will be conducted prospectively among hemodialysis patients at the Hemodialysis Unit, Hospital Kuala Lumpur (HKL), and the Hemodialysis Affiliated Centers of the University Malaya Medical Centre (UMMC). The selected patients will be followed for a period of 12 months. The estimated sample size using a power of 0.95 and 95% confidence interval was 56 patients.

$$n>={\left\{\begin{array}{c} Z_{\alpha /2}+Z\beta \\ ES \end{array}\right\}}^{2}$$

n = sample size

Z = statistic for level of confidence, using a 95% confidence interval (so Z = 1.96)

α = 0.05

β = type 11 error

ES = Effect size, δ / σ

δ = A difference in population means

σ = Standard deviation of difference in the response of matched pairs

Therefore, by using value of δ = 0.9 and σ = 1.84 from similar previous study on chronic illness patient [21].

n = 56

Study of a continuous response variable from matched pairs of study subjects. Prior data indicate that the difference in the response of matched pairs is normally distributed with standard deviation 1.84. If the true difference in the mean response of matched pairs is 0.9, we will need to study 56 pairs of subjects to be able to reject the null hypothesis that this response difference is zero with probability (power) 0.95. The Type I error probability associated with this test of this null hypothesis is 0.05.

**≈** 56 ± 25% * (to compensate for drop off or incomplete data)

≈ 70 respondents

*considering dropout rate of 25%, 14 patients were added; therefore total will be 70 patients altogether.

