### Study strengths & limitations

The limitation of this study is that it needs to be conducted as a pre-post study due to ethical consideration from the study site. Moreover, patients outcomes will be measured through questionnaire, recall bias and social-desirability bias may occur. Another limitation is the selection of 25% as the dropout rate for current study. As ESRD patients are high risk patients with high mortality and morbidity rates, an addition of 25% drop out rate to the total number of sample size may be an underestimation. Moreover, as the patient adherence will be measured using GMAS score, there is potential for overestimation of medication adherence and susceptibility to manipulation. However, patient clinical outcomes will be monitored to estimate an overall medication adherence rate. Nevertheless, medication adherence rate is susceptible to under or overestimation. The strength of this study is that it will be conducted in multicenter sites.

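### The 25% dropout allowance is calculated as 56 × 1.25 = 70 instead of 56 / 0.75 = 75, so 70 enrolled covers 20% dropout; a real but minor arithmetic error

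*Protocol article*

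**What the plan says.** All of this comes from the protocol article.

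- **Target (Study design).** "The estimated sample size using a power of 0.95 and 95% confidence interval was 56 patients". The paragraph adds that "we will need to study 56 pairs of subjects to be able to reject the null hypothesis" at that power.
- **Inputs (Study design).** The mean paired difference and the standard deviation of the differences are set "by using value of δ = 0.9 and σ = 1.84 from similar previous study on chronic illness patient [21]". The test is two-sided, since the formula uses the α/2 quantile with the value 1.96, and "The Type I error probability associated with this test of this null hypothesis is 0.05".
- **Inflation (Study design).** The stated purpose of the increase is to make up for dropout or incomplete data, and the calculation reads: "considering dropout rate of 25%, 14 patients were added; therefore total will be 70 patients altogether".
- **Total (abstract, Method and design).** "A total of 70 patients will be recruited".
- **Limitation (Study strengths & limitations).** Because these patients have high mortality and morbidity, "an addition of 25% drop out rate to the total number of sample size may be an underestimation".

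**The concern.** A dropout rate is a fraction of the patients enrolled. To end with *n* evaluable patients after losing a fraction *d*, one enrols *n*/(1 − *d*). The plan instead enrols *n*(1 + *d*), which always falls short of the target at rate *d*. The three published figures (70 enrolled, 25% dropout, 56 pairs) therefore cannot all hold.

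The comparisons of adherence and quality of life before and after the intervention are planned as paired tests. In such a test a patient without a final assessment supplies no pair, so the number of completers sets the power directly. A reader who relies on the paragraph would believe that power of 0.95 is protected against a 25% loss, when the enrolment figure protects 56 pairs only up to a 20% loss.

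**Working it through.** **Inputs**, all from the Study design section: α = 0.05 two-sided (z = 1.960); power 0.95 (z = 1.645); δ = 0.9; σ = 1.84; required pairs 56; dropout 25%; total 70.

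**Step 1. Reproduce the 56.** The effect size is 0.9/1.84 = 0.489. The printed formula gives

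n = ((1.960 + 1.645)/0.489)² = 54.3, so 55 pairs.

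The exact paired t-test (noncentral t) gives power 0.949 at 56 pairs and 0.952 at 57, so strictly it needs 57. The stated 56 lies between the two answers and is accepted here.

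**Step 2. Reproduce the 70.** 56 × 0.25 = 14, and 56 + 14 = 70. The stated total follows exactly from multiplying by 1.25.

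**Step 3. Apply the stated dropout to the stated total.**

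- Pairs left at 25% loss: 70 × 0.75 = 52.5, that is 52 or 53, which is 3 to 4 below 56.
- Loss that 70 can absorb while keeping 56 pairs: 14/70 = 20%.
- Enrolment that keeps 56 pairs at 25% loss: 56/0.75 = 74.7, so 75. Check: 75 × 0.75 = 56.25.

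**Step 4. Size the effect on power** (δ = 0.9, σ = 1.84, two-sided 0.05). The exact figure is the noncentral-t power; the normal figure is Φ(0.489 × √n − 1.960).

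| Pairs | Dropout from 70 | Exact paired t-test | Normal formula |
|---|---|---|---|
| 56 | 20.0% | 0.949 | 0.955 |
| 55 | 21.4% | 0.945 | 0.952 |
| 53 | 24.3% | 0.938 | 0.945 |
| 52 | 25.7% | 0.933 | 0.941 |

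Between 56 pairs and 52 to 53 pairs, the exact power falls by 0.949 − 0.938 = 0.011 to 0.949 − 0.933 = 0.016. At 52 pairs, the difference detectable with power 0.95 is 0.94 by the exact test, instead of 0.90.

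**The case against.** **The effect is slight.** This stands. Power of 0.95 is a high target, and at the planned 25% loss power stays above 0.93. By the exact test it remains at or above 0.90 down to 46 pairs, a loss of 24/70 = 34%. A reader might infer that the study is underpowered. The documents do not support that: nothing in a shortfall of 3 to 4 pairs would change what this single-group study can conclude.

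**The 20% limit is not a sharp threshold for power.** This also stands. It is the limit for keeping the count of 56. By the printed formula 55 pairs are enough, and 70 enrolled supplies them up to a loss of 15/70 = 21.4%. By the exact test 56 pairs is already a shade under 0.95. It would be too strong to say that any loss above 20% takes power below target.

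**The protocol already warns that the allowance may be too small.** This stands in part. The limitation tells readers that 70 may not be enough, but it questions whether 25% is a realistic rate. It takes for granted that 70 covers 25%, so it does not correct the division. A reader might go on to quote power at 30% or 40% dropout as the cost of this error. Those figures answer the separate question of whether 25% is realistic.

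**The 25% might be only a mark-up on 56.** The text describes the method openly as an addition, and as a mark-up 25% is correct. However, the same sentence calls the figure a dropout rate, and the limitations section does so too. On that wording the total is wrong.

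**Conclusion.** The point holds as a minor arithmetic error. The enrolment of 70 corresponds to 20% dropout, not 25%. At 25% it leaves 52 to 53 pairs, with power 0.933 to 0.938 by the exact paired t-test (0.941 to 0.945 by the printed formula) instead of about 0.95. The loss is 1 to 2 percentage points.

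The dropout arithmetic needs no assumption beyond the plan's own 56, 25% and 70. The powers rest on δ = 0.9 and σ = 1.84, which come from a cited study that is not available here, and on a paired t-test, although the Statistical analysis section also allows the Wilcoxon signed-rank test. Uncertainty in those inputs may well outweigh a change of 1 to 2 points, which is a further reason to treat this as a correction of a published figure and not as a flaw in the design.

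**What to change.** In the Study design section, drop the claim that 70 makes up for 25% dropout and write instead, for example:

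> Enrolling 70 patients provides 56 evaluable pairs at 20% dropout (power about 0.95). At 25% dropout it provides about 52 pairs (power about 0.93).

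This costs only wording. The total in the abstract stays at 70, and the stated power at 25% dropout becomes slightly less favourable.

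If the sponsor prefers to keep both 25% dropout and 56 pairs, the matching enrolment is 75. That means 5 more patients and a change of the total in the abstract and in the Study design section.

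The caution in the limitations section, that the allowance may be too low, stays true and can remain. It need only refer to whichever rate is finally stated.

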#### Participants

All patients aged 18 years or over undergoing hemodialysis treatment (thrice a week) for at least 3 months, and able to communicate in English or Malay, will be included in the study. Patients who have had any major surgical interventions in the previous three months, or have malignancies, cognitive impairment, dementia, active psychosis, or major hearing impairment, or are pregnant or breastfeeding, will be excluded.

#### Patient selection

A simple random sampling technique with a research randomizer, an online tool, will be used to recruit potential patients [22]. The list of all hemodialysis patients will be entered into the research randomizer to generate random numbers to assign to patients for selection [23]. This method of computer-generated simple randomization can minimize the risk of selection bias, as patients will be selected by chance [24]. All demographic data of the selected patients such as age, gender, past medical & medication history, dialysis history, medications prescribed (name, dose, frequency, route, duration of the drug) will be obtained from electronic health records. Once all potential patients are selected, a written, informed consent will be taken from the patients prior to participation.

#### Patient centered pharmacist care

This study will implement a combination of two methods of patient centered pharmacist care, medication review and motivational interviewing. MR helps in identifying, resolving, and preventing drug related problems. While MI is a collaborative communication approach between the pharmacist and patient to stimulate motivation to improve medication adherence.

### Outcomes measured

#### Primary outcome

Measuring the number of medication-related problems. All medication-related problems will be classified using the Pharmaceutical Care Network Europe (PCNE) classification version 9.00, which was last updated in June 2019 [25]. This is an established system for medication-related problem classification. With it, medication-related problems are categorized into nine primary domains for DRP causes. This tool has been validated to measure medication related problems among chronically ill patients [26]. Medication discrepancies are categorized in Table 1. Identification of medication record discrepancies included in this study follows previous literature [27, 28].

**Table 1 pone.0263412.t001:** Medication record discrepancy.

Unintentional Discrepancy: medication change made either inadvertently or deliberately by the patient without the knowledge of the health care team. Undocumented Intentional Discrepancy: medication change made by another healthcare professional but not listed on the medication record. Subcategories include: ● omission (medications being taken by the patient but not listed in the medication record) ● commission (medications no longer being taken by the patient but still listed on the medication record) ● wrong drug ● wrong dose ● wrong frequency ● dose/schedule not listed

Source: Medication record discrepancy [22,23].

#### Secondary outcomes

Measuring the number of adherences, quality of life and clinical outcomes.

*a) General Medication Adherence Scale (GMAS)*. A novel GMAS will be used to measure the adherence. This scale consists of 11 questions which measure the adherence in three domains: the first 5 questions measure nonadherence due to patient behavior, followed by 4 questions measuring the comorbidity and pill burden related nonadherence, and the final 2 questions measuring cost-related nonadherence. Each question has 4 possible answers—always, mostly, sometimes, and never—which will be awarded a score of 0, 1, 2 or 3, respectively. A cumulative medication adherence score of 30 to 33 will be considered as high adherence, followed by a score of 27 to 29 as good adherence, a score of 17 to 26 as partial adherence, a score of 11 to 16 as low adherence and lastly poor adherence for patients scoring 0 to 10. This adherence tool has been validated to measure medication adherence among chronically ill patients [29].

*b) Kidney disease quality of life-36*. A validated KDQOL-36 questionnaire will be used to measure the quality of life among HD patients. KDQOL-36 is a disease-specific instrument that has been widely used to assess the HRQOL in ESRD patients. It contains a subset of the KDQOL-SF items, including the SF-12 items and 24 items to obtain three kidney disease-specific scales, which are burden of kidney disease (4 items), effects of kidney disease on daily life (8 items), and symptoms or problems (12 items). The three disease-specific subscales can be summated into the kidney disease component summary score. The SF-12 is developed using a subset of the SF-36 items. It will generate two summary scores, which are the physical component summary (PCS) and mental component summary (MCS). All these scores range from 0 to 100, with higher scores reflecting better health. In this study, the Malay version of the KDQOL-36 questionnaire will be used, as it is validated [30].

*c) Clinical outcomes*. Clinical outcomes such as blood glucose level, calcium, phosphate, hemoglobin and LDL levels will be obtained from the computer and medical records at the HD unit. These lab parameters will be measured at the baseline, 6^th^ month and the final of the study. The changes in the value of the clinical parameters will be analyzed to find if there is any significant difference after the intervention.

This analysis is important as it acts as surrogate marker for adherence and can be corelated with GMAS scores to show that lab parameters will be within the desired range if patient adherence is improved.

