#### a) Medication review

MR is a well-structured method to optimize medication use and improve health outcomes among patients [31]. The researcher will examine patient medical records and interview patients to identify patient medication discrepancies and medication-related problems. Any medication issue related to a patient’s medicine-taking behavior and use of medicine in the context of their clinical condition will be recorded. The PCNE version 9 and kidney-related clinical practice guidelines will be used as guides. All the recorded medication problems will be discussed with relevant physician. The changes done by the physician will be notified to the researcher and can be tracked in the following follow up.

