### Study procedure and follow up

Once informed consent is obtained from the eligible patients at the first month’s visit, patients’ medication adherence, QOL and lab results—mainly the calcium, phosphate, hemoglobin, lipid profile, and glycosylated hemoglobin levels will be assessed. A medication review will also be performed. The updated list and observations/recommendations will be provided to the physician in charge. The medical records will be reviewed in the following six months to determine whether individual discrepancies have been corrected and whether MRP recommendations have been accepted by the prescriber. Motivational interviewing will be conducted in 3 sessions, in the 3^rd^, 6^th^ and 9^th^ months. Each session will last approximately 15 to 20 minutes for each patient. Only the first session will be done face to face (during the patient’s scheduled dialysis day) to build a good relationship with the patient, while the second and third sessions will be conducted over the phone to minimize close contact with the patients during the COVID-19 outbreak period. This method has proven its efficacy in previous research [37] and ensures safety for both patients and the researcher. The number of sessions to motivate and improve medication adherence has been set at three, as the optimal number is not known [38–40]. At the final visit (12 months), the medication review will be performed, medication adherence, QOL score and lab parameters will be assessed. The pre-post results will be checked for significance in improvement using the software package Statistical Package for Social Sciences (SPSS) Version 26.0. The results will be evaluated to check if there are any significant changes in the number of medication-related problems, adherence and QOL at the end of patient-centered pharmacist care. The summary of study procedure is shown in Fig 1.

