**Fig 1 pone.0263412.g001:**
[figure not shown]
Flow chart summary of study procedure.

All the recruited patients only can do their hemodialysis in the registered respective HD unit. They must strictly follow to their HD schedule, check blood sample every 3 months and reviewed by the nephrologist. This is the practice in the HD unit (at the study site) included. Patients’ movement control can be easily monitored, and the lab results will be captured in their medical records appropriately. Hence, missing data is avoided. As the interventions done every 3 months, the researcher can get the sufficient information from the patients and medical records. Patient missed appointments due to logistic reasons will be rescheduled within one week interval. However, missed appointment for more than 3 times due to hospitalization or changes in disease state, the case will be discussed with physician and co-researchers. Based on the expert opinion, decision on exclusion of the patient will be made.

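### The labs are hypothesised to reach the desired range, but change in value and a correlation with GMAS cannot show this or stand in for adherence, and the glycaemic measure is not fixed

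*Protocol article*

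**What the plan says.** **The hypothesis.** The Discussion part of the abstract expects higher adherence and quality-of-life scores "as well as achieving the clinical lab parameters within the desired range".

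**The analysis.** Secondary outcomes, item c, states that "The changes in the value of the clinical parameters will be analyzed to find if there is any significant difference after the intervention". It then calls the lab analysis a surrogate for adherence and says that it "can be corelated with GMAS scores to show that lab parameters will be within the desired range if patient adherence is improved". Study strengths & limitations returns to this: having conceded that GMAS may overstate adherence, it offers the monitored clinical outcomes as a way of estimating overall adherence.

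**The other route to the labs.** Under Medication review, recorded problems are taken to the physician, and "The changes done by the physician will be notified to the researcher and can be tracked in the following follow up".

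**The lab list.** Secondary outcomes says "Clinical outcomes such as blood glucose level, calcium, phosphate, hemoglobin and LDL levels will be obtained", and the Method and design part of the abstract names the same five. Study procedure and follow up says "mainly the calcium, phosphate, hemoglobin, lipid profile, and glycosylated hemoglobin levels will be assessed".

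**The times.** Secondary outcomes gives baseline, month 6 and the end of the study. Study procedure and follow up describes labs at the first and the 12-month visits. The text after Fig 1 says that patients "check blood sample every 3 months and reviewed by the nephrologist".

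**The concern.** Being in range and having changed are different questions. Where the desired range has both a lower and an upper limit, as it may for calcium or hemoglobin, some patients can start too low and others too high. If both groups move into range, their changes cancel in the mean. In the other direction, the mean can shift significantly while no more patients, or fewer, are in range. A correlation between lab values and GMAS does not help, because association says nothing about where the values lie relative to the limits.

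The adherence reading has a separate problem. The package under study includes a medication review meant to lead to prescribing changes. Labs can respond to those changes with adherence exactly as before, and there is no control group to separate the two routes. This matters because the labs are the safeguard that the article offers against inflated self-report.

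Finally, blood glucose and glycosylated hemoglobin are different measurements. With both named, the glycaemic outcome is not settled.

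**Working it through.** **Does the plan give a figure to reproduce?** Not for the labs: there are no target ranges, lab SDs or baseline in-range shares. The only computed figure is the sample size of 56 pairs. It reproduces closely: ((1.96 + 1.645) × 1.84 / 0.9)² = 54.3, so 55, and a noncentral-t check gives power 0.949 at 56. It has no bearing on this point.

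**Illustration.** All lab inputs are assumed. The lab is put on a standardised scale with desired range −1 to +1 and normal values, and the baseline to month-12 correlation is 0.5. The share in range is Φ((1 − μ)/σ) − Φ((−1 − μ)/σ).

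*Change from both sides (mean stays at 0).* The number of completers is 70 × 0.75 = 52.5, taken as 52.
- Baseline SD 1.5: Φ(0.667) − Φ(−0.667) = 49.5% in range.
- Month-12 SD 1.0: Φ(1) − Φ(−1) = 68.3%.
- Month-12 SD 0.8: Φ(1.25) − Φ(−1.25) = 79%.
- In simulation, a paired t-test on the change rejects about 5% of the time in both cases, its false-positive rate. A Wilcoxon test does the same. McNemar's exact test on in-range status rejects about 45% and 88%.

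*Mean shift without better attainment.* SD is 1 at both times, so the SD of the difference is √(2 × (1 − 0.5)) = 1. With 56 patients the noncentrality for a shift of 0.5 is 0.5 × √56 = 3.74, and the paired t-test has about 96% power.
- Mean from +0.25 to −0.25: Φ(0.75) − Φ(−1.25) = 66.8% before, and by symmetry 66.8% after.
- Mean from 0 to −0.5: 68.3% before, Φ(1.5) − Φ(−0.5) = 62.5% after.

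*Patients starting off-centre.* This is the case that favours mean change (52 completers, simulated).

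| Mean | SD | In range | t-test rejects | McNemar rejects |
|---|---|---|---|---|
| 0.5 to 0 | 1.5 to 1.0 | 47% to 68% | about 75% | about 53% |
| 1.0 to 0.4 | 1.5 to 1.2 | 41% to 57% | about 87% | about 32% |
| 1.5 to 0.75 | 1.5 to 1.5 | 32% to 44% | about 94% | about 22% |

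A significant mean change can therefore go with higher, equal or lower attainment, and a null mean change can go with a large gain. Neither analysis is uniformly the more powerful.

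**Side-by-side reading.**
- *Adherence.* Medication review gives a path from intervention to prescription to lab that bypasses adherence. Secondary outcomes and Study strengths & limitations read lab movement as evidence of adherence.
- *Lab lists.* Calcium, phosphate and hemoglobin agree, and LDL is part of a lipid profile. Only the glycaemic measure differs.
- *Times.* Three-monthly samples in the records can supply baseline, month 6 and month 12.

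**The case against.** Several objections have force.

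- **No test is named for the labs.** The article assigns paired t-tests or Wilcoxon tests to adherence and quality of life only. A reader might infer that a paired t-test is the planned lab test, but the article does not say so, and the choice may sit in the full protocol. This stands. The point is about the stated target of the analysis, change in value, and not about a particular test.
- **The zero-mean-change illustration is favourable to the concern.** It puts the mean exactly mid-range and shrinks the SD a good deal. With month-12 SD 1.3 instead, the t-test rejects 5% and McNemar only 7%, and the off-centre cases favour mean change clearly. This also stands, so the change in value should not be demoted to description.
- **The times could be read as contradictory.** The documents do not support that. The procedure section omits month 6 without excluding it, routine sampling covers it, and the flow chart is not shown.
- **The lists are hedged.** Both are introduced as partial, and the abstract and the outcome definition agree on blood glucose. A reader might infer that the measure will be picked after the data are seen. Nothing in the article indicates this. The inconsistency itself remains.
- **The limits of the adherence check are partly disclosed.** The limitations section grants that adherence may be under- or overestimated, and the correlation is offered as something that can be done. Prescribing changes weaken the check without making it worthless. What does not stand is the surrogate claim, or the claim that the correlation shows range attainment.

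**Conclusion.** The concern holds in a limited form. The hypothesis concerns the desired range, while the stated analysis concerns change in value plus a correlation. For parameters with two limits these can give opposite answers. The logic needs no assumed number; the sizes rest wholly on the assumed standardised lab, range, SDs and correlation, and show only what is possible: a rise from 49.5% to 68.3% in range that a paired t-test on the change picks up no more often than chance, or a shift detected with about 96% power while attainment stays at 66.8% or falls to 62.5%.

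It would go too far to say that the lab results can neither support nor undermine the hypothesis. When patients start mostly on one side of the range, mean change is informative and can be the more powerful analysis.

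The surrogate role is not supported, because the medication review gives the labs a second route to change. The glycaemic measure needs to be settled; the rest of the lab list and the sampling times can be reconciled. These are secondary outcomes, and the primary outcome, the number of medication-related problems, is untouched. The change is worth making but does not threaten the trial.

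**What to change.** 1. Keep the change in value. For each parameter with a desired range, add an in-range (yes/no) outcome with limits fixed before analysis, compared between baseline and month 12 by McNemar's test, or by a repeated-measures logistic model that includes month 6. Base any statement about the desired range on that analysis. Alternatively, restate the hypothesis as mean change.
2. Delete the claim that the correlation with GMAS shows range attainment, describe the correlation as exploratory, and drop the word surrogate. Make the matching sentence in Study strengths & limitations consistent with this.
3. Report the tracked prescription changes descriptively beside the lab results. Do not restrict to patients without such changes: they are a post-baseline consequence of the intervention, so restriction can introduce selection bias and would shrink a cohort of at most 70.
4. Name one glycaemic measure in the abstract, Secondary outcomes, and Study procedure and follow up.

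The cost is some rewording and a little more analysis of data already collected. The in-range comparison can have less power than mean change when patients start mostly on one side of the range, which is the reason to keep both.
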